## Abstract

**Introduction:**

Hypertension is a common risk factor for cardiovascular disease. Transcutaneous electrical acupoint stimulation (TEAS) may be effective for hypertension, but the evidence remains limited. The aim of this study is to evaluate the effectiveness and safety of the smart phone-based TEAS as adjunctive therapy for hypertension.

**Methods and analysis:**

This study is a 52-week cluster randomised controlled trial with 1600 hypertension patients in 32 community health service centres. Patients who meet the inclusion criteria will be randomised into usual care group or TEAS group in a 1:1 ratio. All patients will be provided with usual care as recommended by the guidelines. In addition to this, patients in the TEAS group will receive non-invasive acupoint electrical stimulation for 30 min at home, 4 times weekly for 12 weeks. The primary outcome will be the mean difference in the changes in office systolic blood pressure from baseline to 12 weeks between TEAS and usual care groups. Secondary outcomes will include the change of mean diastolic blood pressure, proportion of patients with controlled blood pressure (blood pressure <140/90 mm Hg), proportion of patients taking antihypertensive drugs, change in number of antihypertensive drugs and changes in 12-item Short-Form. Tertiary outcomes will include change in body mass index, change in waist circumference, physical activity and medication adherence. Safety outcomes will be any serious adverse events and clinical events.

**Ethics and dissemination:**

This study has been approved by ethics committee of Beijing University of Chinese Medicine (No. 2020BZHYLL0104). Written informed consent will be obtained from all patients before randomisation. Trial results will be disseminated in peer-reviewed publications.

**Trial registration number:**

ChiCTR2000039400.

Strengths and limitations of this studyIn this randomised controlled trial, a large population of 1600 hypertension patients will be recruited from 32 community health service centres.This community-based cluster trial could lower the risk of contamination as much as possible and overcome the traditionally low detection of hypertension in hospital-based studies.The smart phone-based transcutaneous electrical acupoint stimulation (TEAS) can be received at home by the patients themselves to reduce the burden of logistics and lost wages.The background of TEAS software would recognise patients with poor compliance real timely and remind them of receiving TEAS to improve the adherence rate.Surrogate outcome, not clinical event, is used as primary outcome and blinding for patients was not feasible in this study.

## Introduction

Cardiovascular disease is the most common cause of premature death and disability worldwide, and hypertension is the most common risk factor for cardiovascular disease.^1^ WHO suggested that the global prevalence of hypertension was 20% for females and 25% for males.^2^ Moreover, according to the latest American College of Cardiology/American Heart Association guideline,^3^ the prevalence of hypertension increased to nearly 50%.^4–6^ Hypertension accounted for 9.4 million deaths and 7.0% of global disability-adjusted life-years.^7^ The total costs of hypertension will increase to an estimated US$274 billion by 2030.^8^

Lifestyle modifications are recommended by all guidelines in different countries,^3 9 10^ while most patients are unable to sustain lifestyle changes. Antihypertensive drugs are widely prescribed for patients with hypertension. However, fewer than 20% of patients with hypertension have their blood pressure controlled.^10^ The reasons for low control rate of blood pressure include the poor adherence of medicine and the burden of logistics. Identifying non-pharmaceutical therapy with good adherence that can be done at home is urgently needed to reduce blood pressure in patients with hypertension.

Acupuncture, as a non-pharmaceutical therapy, was used for several cardiovascular diseases.^11 12^ Previous studies indicated that acupuncture could decrease blood pressure^13 14^ and a recent systematic review found that acupuncture as adjunctive therapy may be effective for hypertension.^15^ However, acupuncture also has the same limitation of logistical burdens as the antihypertensive drugs. Transcutaneous electrical acupoint stimulation (TEAS), a non-invasive acupuncture therapy, has a similar effect with acupuncture^16–18^ and can be performed at home by the patients themselves. Our pilot study found that TEAS added to usual care for patients with hypertension was feasible and may be a potential treatment option.^19^ The aim of this cluster randomised controlled trial is to evaluate the effectiveness and safety of the smart phone-based TEAS as adjunctive therapy for hypertension.

## Methods

### Study design

This two-arm, open-label, cluster randomised controlled trial will be conducted at 32 community health service centres in China. The total trial period was 52 weeks, including 12 weeks of treatment and 40 weeks of follow-up. The study protocol (version number: 2.0; 13 June 2020) has been registered on Chinese clinical trial registry (No. ChiCTR2000039400). The protocol will be reported following the SPIRIT guideline.^20^
Figure 1 shows the flow diagram of the trial.

**Figure 1 F1:**
[figure not shown]
Flow diagram. TEAS, transcutaneous electrical acupoint stimulation.

### Study recruitment

There are 16 districts and 346 community health service centres in Beijing, China. Of them, 32 community health service centres (online supplemental file 1), 2 centres in each district, will be recruited through Beijing Administration of Traditional Chinese Medicine and Beijing Association of Acupuncture-Moxibustion. Patients will be diagnosed as hypertension according to the European guideline^9^ and Chinese guideline.^10^ About 50 patients will be enrolled in each centre by their family doctors. The family doctors will conduct a preliminary screening to exclude ineligible patients, then the office blood pressure will be measured in the consulting room by clinical research coordinators to determine whether the patients will be finally included or not.

10.1136/bmjopen-2021-058172.supp1Supplementary data

### Participants

#### Inclusion criteria

Office systolic blood pressure (SBP) from 140 to 159 mm Hg and/or diastolic blood pressure (DBP) from 90 to 99 mm Hg for patients who did not take antihypertensive drugs previously, or office SBP from 120 to 159 mm Hg and/or DBP from 80 to 99 mm Hg for patients who did not change antihypertensive drugs at least 1 month.Aged between 18 and 65 years (male or female).Answering and completing the questionnaires.Using smart phone.Written informed consent.

#### Exclusion criteria

Other diseases that can affect the blood pressure, including but not limited to diseases of renal parenchyma, renal artery stenosis, obstructive sleep apnoea syndrome, and primary hyperaldosteronism.Receiving medicines that affect blood pressure except antihypertensive drugs in last month, including but not limited to glucocorticoids and central nervous system inhibitors.Contraindications for the use of acupoint stimulators: wearing a pacemaker and other implanted medical devices; epilepsy; scars, bruises, scratches or inflammation on the skin of the acupoints; allergic to electrodes.Uncontrolled diabetes (HbA1c≥6.5%).Drug or alcohol abuse.Pregnant or breast feeding.Participated in other clinical trials in the past 3 months.

### Randomisation and masking

The unit of randomisation will be the community health service centres. Thirty-two centres will be randomised to either TEAS or usual care group in a 1:1 ratio with a central randomisation system. All patients within the defined centre will receive the same allocated treatment. Each centre will not be randomised until total 50 patients are recruited to avoid selection bias. The randomisation sequence will be generated by an independent statistician with the Stata V.12.0 software and will be stratified by districts. The patients and the acupuncturists who teach patients how to locate acupoints and to receive TEAS at home will not be blinded. However, the family doctors who prescribe antihypertensive drugs, outcome assessors and statisticians will be blinded.

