### Sample size calculation

The effective sample size (ESS) of 392 patients in each group is calculated for SBP on the basis of an alpha level of 0.05 (two sided), a beta level of 0.80, an expected between-group difference of 6 mm Hg,^19^ an SD of 10 mm Hg and a superiority margin of 4 mm Hg,^28^ if randomisation takes place at the individual level. With average 40 patients per community and an intracluster correlation of 0.01,^29^ the ESS should be multiplied by a design effect of 1.39, leading to 560 patients in 14 communities per group (1120 patients in 28 communities in total). As our experience suggests that up to 10% of the randomised communities and up to 20% of the recruited patients may drop out of the study, we aim to recruit 32 communities (16 per group) including 50 patients each, resulting in a target sample size of 1600 recruited patients in total (800 per group).

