### Statistical analysis

A full analysis set, a per-protocol set and a safety set will be used in this trial. The full analysis set will consist of all randomised patients according to the intention-to-treat principle. The full analysis set will be the primary analysis, and all analyses will be conducted for this population if not otherwise stated. The per-protocol set will include those who complete all follow-ups on time and without major violations. Major violations include but are not limited to not ineligibility according to the inclusion and exclusion criteria, receiving medicines that affect blood pressure except antihypertensive drugs, or not completing ≤38 sessions TEAS (80% of prespecified 48 sessions). The per-protocol set will be the secondary analysis set and will be used for the sensitivity analyses for the primary outcome. All those who receive at least one session of TEAS will be defined as the safety set, which is used for the safety analyses.

Baseline characteristics will be summarised by groups. Continuous variables will be described using the mean (SD), or the median (IQR) if the normality assumption is violated. Categorical variables will be described using the frequency (percentage). The significance level of superiority test will be set at one-sided 0.025 for the primary outcome. The significance level will be set at two-sided 0.05 for secondary outcomes. All analyses will be carried out using SAS V.9.3.

The change from baseline in office SBP at week 12 will be analysed by a mixed-effect model using baseline value as a covariate, treatment group as a fixed effect, and community and interaction between community and treatment as random effects. Multiple imputation will be used for missing data.^30^ For the secondary and tertiary outcomes, continuous variables will be compared at all follow-up time points using a mixed-effect model with repeated measurement methods. If there is a normality violation in the continuous variables, a transformation will be performed before the test. Categorical variables will be compared using a generalised linear mixed-effect model. The consistency of treatment effects on the primary outcome will be explored in predefined subgroups, including sex, education and taking antihypertensive drugs or not and urban or rural community.

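### Centres are randomised within districts, but the primary model omits district and spends a random term on an inseparable community-by-treatment effect; if districts differ, the test is somewhat conservative

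*Protocol article*

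**What the plan says.** All references are to the protocol article.

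- **Study recruitment:** "There are 16 districts and 346 community health service centres in Beijing, China"; of these centres, "2 centres in each district, will be recruited".
- **Randomisation and masking:** "Thirty-two centres will be randomised to either TEAS or usual care group in a 1:1 ratio", and the sequence "will be stratified by districts". All patients of a centre get that centre's treatment.
- **Statistical analysis:** the week 12 change in office SBP is analysed by a mixed model "using baseline value as a covariate, treatment group as a fixed effect". The full set of group and random terms is "treatment group as a fixed effect, and community and interaction between community and treatment as random effects". District is not among them, nor is it named for the secondary and tertiary outcomes.
- **Sample size calculation:** the net difference to detect is 6 minus 4 mm Hg with SD 10 mm Hg, 40 patients per community and ICC 0.01. The design effect of 1.39 takes no credit for stratification.

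The article does not use the word pair. One centre per arm in each district follows only if the 1:1 ratio is kept inside each two-centre stratum, which is the usual result of such stratification but is not stated.

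**The concern.** The stated model does not match the randomisation in two ways.

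First, with one TEAS and one usual care centre per district, a district's own level cancels from the treatment contrast. The true sampling variance of the effect therefore excludes between-district variation. A model without district still counts that variation as part of the community variance, so it enters the reported standard error. The confidence interval is then wider than the design warrants, and the test against the 4 mm Hg margin rejects less often than its nominal level.

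Second, a community-by-treatment variance can be estimated only if communities contain both arms. Here each has one. The two random terms have the same levels and only their sum is identified. The district is the smallest unit in which both arms occur, and it is the one left out.

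At stake are the width of the primary interval and some power in a trial that must show more than 4 mm Hg when it expects 6.

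**Working it through.** **Inputs from the article:** 16 districts with 2 centres each; 32 centres 1:1; 40 analysed per centre; SD 10; ICC 0.01; net difference 6 − 4 = 2 mm Hg; one-sided 0.025.

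**Assumed, because the article does not give it:** the share *s* of between-centre variance that is due to district.

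**1. The plan's own figure.** The section gives "an alpha level of 0.05 (two sided), a beta level of 0.80"; the 0.80 is read as power.
- n per group = 2 × (1.960 + 0.842)² × 10² / 2² = 392.4, against 392 stated.
- Design effect = 1 + 39 × 0.01 = 1.39. Then 392 × 1.39 = 544.9, or 13.6 communities of 40, hence 14 communities and 560 patients per group.
- 40 / 0.80 = 50 per centre; 28 / 0.90 = 31.1, hence 32 centres and 1600 patients.

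The sample size reproduces.

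**2. Standard errors.** Between-centre variance is 100 × 0.01 = 1. The within-centre variance of a centre mean is 100 × 0.99 / 40 = 2.475.
- Reported without district (expected): √[2 × (1 + 2.475) / 16] = 0.659, whatever *s* is.
- True: √{2 × [(1 − *s*) + 2.475] / 16}.

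| *s* | True SE | Reported / true |
|---|---|---|
| 0.10 | 0.650 | 1.015 |
| 0.25 | 0.635 | 1.04 |
| 0.50 | 0.610 | 1.08 |
| 0.75 | 0.584 | 1.13 |

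**3. Type I error and power.** Centre means were simulated (200,000 runs, 16 complete pairs of equal size) and analysed in three ways:
- no district, t with 30 df;
- fixed district, a paired t with 15 df;
- random district, equal to the paired analysis when the district variance estimate is positive and to the analysis without district when it is zero.

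| *s* | Type I error: none / fixed / random | Power: none / fixed / random |
|---|---|---|
| 0 | 0.025 / 0.025 / 0.031 | 83.5 / 80.9 / 85.0% |
| 0.10 | 0.023 / 0.025 / 0.030 | 84.0 / 82.1 / 85.8% |
| 0.25 | 0.021 / 0.025 / 0.029 | 84.6 / 83.9 / 86.8% |
| 0.50 | 0.018 / 0.025 / 0.028 | 85.4 / 86.6 / 88.5% |
| 0.75 | 0.014 / 0.025 / 0.026 | 86.2 / 89.2 / 90.4% |

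Power without district also rises with *s*. The stratified design lowers the true variance of the estimate even when the analysis ignores it. Fixed district effects overtake the model without district only above *s* of about 0.35.

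**4. Other scenarios.**
- 14 complete pairs, ICC 0.01, *s* = 0.50: about 80% without district, about 84% with random district.
- ICC 0.03 (assumed), 16 pairs, *s* = 0.50: about 67% without district, against 76% (fixed) and 77% (random). Type I error without district is 0.012.

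**The case against.** The strongest reply is that little is lost. The effect estimate is unaffected and the error is on the safe side. The sample size uses the full design effect of 1.39, so the planned 80% power never relied on a district term. With all 16 pairs at 40 per centre, the planned model keeps about 84% to 86%. Baseline SBP is already in the model and may absorb part of any district difference. The analysis plan is not shown and may add district. All of this stands as a limit on the size of the point. It does not remove it: the article writes the primary model out term by term, district is not in it, and one term that is in it cannot be estimated separately.

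Three stronger readings are tempting, and the documents do not support them.

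- **That power is lost whenever districts differ, and at no cost to recover.** Fixed district effects use 15 of the 30 df. At the planned ICC they lower power by 0.7 points at a share of 0.25 and by 1.9 points at 0.10. A random effect gains 2 to 4 points, but part of this comes from type I error of about 0.026 to 0.030.
- **That modelling district lifts power from 84% to 89% or 94%.** One reaches this by putting the smaller standard errors (0.610 and 0.556, for shares of one half and all) into a 30 df test and comparing with the power at a share of zero. The right comparison holds the share fixed, and a fitted district effect does not in general leave 30 df.
- **That the stated analysis endangers a positive conclusion.** Its type I error is at or below nominal.

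**Conclusion.** The concern holds as a modest point of calibration and efficiency. The stated primary model omits the stratification factor and includes a random term that the design cannot separate from community. If districts differ, its standard error is too large on average and the margin test is conservative. At the planned ICC, for shares of 25% to 75%, that means a standard error 4% to 13% too large, one-sided type I error of 0.021 to 0.014, and about 2 to 4 points of power against a random district effect. The cost grows if the true ICC exceeds 0.01.

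The direction rests on 1:1 allocation being held within each district. The size rests on the assumed district share, on equal centre sizes and complete pairs, and on no absorption of district differences by baseline SBP. The ICC of 0.03 is an assumption, not a figure from the article.

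**What to change.** In Statistical analysis:

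1. Replace the community-by-treatment random term with district as a random effect, with community nested in district.
2. Prespecify a small-sample degrees-of-freedom method, for example Kenward-Roger.
3. State what is done when the district variance is estimated at zero, since dropping the term in that case is what makes the test slightly liberal.
4. Use the same structure for the secondary outcomes.
5. In Randomisation and masking, say whether 1:1 is held within each district.

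If the sponsor prefers to leave district out, the reason should be given.

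A random effect is preferable to fixed district effects for two reasons. It costs less power when districts hardly differ, and when a whole community drops out (up to 10% is allowed for) a fixed effect loses the treatment contrast in that district.

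The cost is wording only, because every centre's district is already known. The statistical downside is some loss of degrees of freedom, or a type I error slightly above nominal when the district variance is estimated at zero. The change should be fixed before unblinding.

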### Interventions

#### Usual care group

All patients will be provided usual care at the respective community health service centre, in conjunction with any ongoing care that they are receiving from their family doctor. Patients at high or very high cardiovascular risk will receive antihypertensive drugs according to the recommendation of the guidelines,^9 10^ including diuretics, β-blockers, calcium channel blockers, angiotensin receptor blockers and ACE inhibitors. The choice of antihypertensive drugs will be individualised, with consideration of patients’ coexisting conditions and adverse effects to the medications. Research team will engage in consistent communication with each patient’s family doctor, including a standard letter conveying the reminder that the doctor is free to implement any additional therapies that are deemed to be appropriate, including increase or decrease the type and dosage of antihypertensive drugs. Research team will also send education materials to all patients. Content will include information about hypertension, its clinical features, epidemiology, diagnostic criteria and treatment options, as well as the role and suggestions of lifestyle intervention in hypertension.

#### TEAS group

In addition to the usual care, the patients in the TEAS group will receive 48 sessions of TEAS treatment (4 times weekly for 12 weeks). TEAS will be performed using a portable instrument (SDP-310, Hwato, Suzhou Medical Appliances, Suzhou, China) with a pair of rounded electrodes (diameter=38 mm) through smart phone. The adhesive electrodes will be applied to the skin as illustrated in figure 2 after the skin sites are cleaned with alcohol to avoid any barrier conduction of the electrical current. The instrument has ten levels of stimulus intensities, and patients asked to increase the stimulus intensity until local, rhythmic contractions of the muscle are obtained without producing pain. According to the previous studies,^16 19 21 22^ bilateral *Hegu* (LI4), *Quchi* (LI11), *Zusanli* (ST36) and *Taichong* (LR3) will be used in our trial. On the first day, the electrodes will be placed at the ipsilateral LI4 and LI11, and the appropriate stimulus intensity will last for 15 min. Then the opposite arm will be stimulated in the same way for another 15 min. On the third day, the ST36 and LR3 will be stimulated for 15 min per leg in the same way. Two pairs of acupoints (LI4-LI11 and ST36-LR3) will be stimulated alternatively every other day. Locations of acupoints are shown in table 1. The acupuncturists will train the patients on how to locate the acupoints and use the instrument face to face. Instructions and acupoint maps will also be provided to help patients to locate the acupoints at home. The patients will be told that the acupoints stimulation can be done when they are leisure at home, like reading the newspaper or watching television. The date, duration and specific acupoints of each acupoint stimuli will be recorded real timely by TEAS software. Thus, the investigator could recognise patients with poor compliance in a timely manner and prompt them to complete the predefined 48 sessions.

**Figure 2 F2:**
[figure not shown]
The instrument and the locations of acupoints.

**Table 1 T1:** Locations of acupoints in the TEAS group

Acupoints	Locations
Taichong (LR3)	On the dorsum of the foot, between the first and second metatarsal bones, in the depression distal to the junction of the bases of the two bones, over the dorsalis pedis artery
Zusanli (ST36)	On the anterior aspect of the leg, on the line connecting ST35 with ST41, 3 cun^*^ inferior to ST35
Hegu (LI4)	On the dorsum of the hand, radial to the midpoint of the second metacarpal bone
Quchi (LI11)	On the lateral aspect of the elbow, at the midpoint of the line connecting LU5 with the lateral epicondyle of the humerus

*One cun (≈20 mm) is defined as the width of the interphalangeal joint of patient’s thumb.

TEAS, transcutaneous electrical acupoint stimulation.

